#### Analysis of secondary outcomes

In the secondary analysis, the same analytical method will be used as in the primary analysis for each test score (mathematics and language) and the continuous outcomes of BMI, sleeping hours, 20m shuttle run, each element of the Flanker test, side-to-side movement, and each SDQ score for mental health. We will use mixed-effects logistic regression for binary data. The covariate of this model is also the same as in the primary analysis. Although the frequency of exercise and playing outside hours constitute ordered data, they will be converted into binary data using a cutoff in the secondary analysis. The cutoff of the frequency of exercise will be between “1–2 days” and “3–4 days”, playing outside hours will be between “30 min-59 min” and “60 min-119 min”. Since the analysis of the secondary outcome is the exploratory evaluation, we will not adjust for the multiplicity of statistical testing.

In the analysis of cognitive function using the Flanker test, participants who fail to reach a correct rate of 50% will be excluded on the assumption that they do not understand the test.

In this study, any imputation will not be performed to missing data due to lost participants or imperfect data collection. The data will be analyzed using STATA V.13.1 (STATA/IC 13.1 for Mac, STATA Corp, [name] College Station, Texas), SAS Software 9.4 (SAS Inc., Cary, NC, USA), and SPSS statistics V.19.0 (IBM SPSS Statistics for Windows, IBM Corp, Armonk, New York).

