### Secondary outcomes

The proportion of obesity and overweight, and the physical fitness function, lifestyle, and mental health, and cognitive function measures between November and December 2018 will be the secondary outcomes. All measures will be obtained in between February and April in 2018 as baseline data.

The researchers and RAs will obtain physical measurements (height and body weight) and physical fitness function test data to establish the baseline in February and at the end of study. The body mass index (BMI) will be calculated, and the proportion of participants classified as obese or overweight using the WHO/CDC criteria will be calculated. Physical fitness function will be assessed by participants’ performance on a 20-m shuttle run and side-to-side jumps.

Participants’ parents or guardians will answer a self-administered questionnaire on lifestyle covering their children’s sleeping hours, exercise habits, time spent viewing television or using video games, children’s household tasks, and their mental and physical health. Children’s physical health condition will be assessed using a five-point Likert scale. The Strengths and Difficulties Questionnaire (SDQ), which has already translated into Mongolian and back-translated, [37] will be used to assess the mental health of the participants. The cut-off values on the SDQ published in the literature and available on the official website for ‘normal,’ ‘borderline,’ and ‘abnormal’ will be adopted. [38]

To assess cognitive function, the Flanker test, a representative cognitive function test specifically assessing inhibitory control of the executive function, will be used. [39] The Flanker test will be administered using a specially-designed app for use on a tablet at school under the instruction of the researchers. The response time and correct rate for 50 tasks, including congruent and incongruent tasks, will be measured. Before the actual test, every student will do a practice test consisting of ten tasks once or twice.

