The intervention will begin in April 2018. Randomized allocation is done in February 2018 and baseline data collection will be done from February to April 2018. The intervention period will be interrupted by summer vacation between the end of June and the beginning of September 2018. The intervention period before summer vacation is the first phase of the intervention and after summer vacation is the second phase of the intervention. Post-intervention data will be collected between November and December 2018. (Fig. 1).

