### Statistical methods

#### Analysis of the primary outcome

The baseline data of the intervention and control groups will be compared. The chi-squared test will be used for binary variables and the t-test will be used for continuous variables. To avoid overestimating the impact of the intervention, an intention-to-treat approach will be adopted to evaluate the impact on the primary and secondary outcomes. In this study, an individual’s data will be analyzed in the originally allocated arm even if the individual moves to a school in another area during study period.

To examine the effect of the intervention while taking the hierarchical structure into consideration, we will use a linear mixed effect model. In this model, the fixed effects are the group (intervention/control), site (Urban/ *ger* or mixed residential), and measurement time point with the following two interaction terms: the interaction between group and measurement time point, and the interaction between the group, measurement time point, and site. The random effects are school and individual. The degrees of freedom will be estimated using Satterthwaite approximation. For the primary analysis, we will compare the participants’ performance on the national year-end examination before and after the intervention using least squares means estimated by the interaction term of the group, measurement time point, and site. The Bonferroni method will be used as a multiplicity adjustment method. A significance level of 0.025 will be set for a two-sided test, and the 95% confidence interval will be calculated.

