#### Subgroup analysis

The effect of the intervention will be further analyzed using four subgroup analyses. The first subgroup analysis will focus on the location of the schools (urban and non-urban areas), the second on gender, and the third on baseline physical fitness performance using the median score on a 20m shuttle run. The fourth subgroup analysis will focus on baseline academic achievement using the total score on the national year-end examination in May 2017 and the median score. The fifth subgroup analysis will be done after excluding participants whose correct rate on the Flanker test is below 80% at either the baseline or endline surveys.

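### Flanker exclusions can depend on endline correct rate, itself an analysed outcome: explicitly under the 80% rule, and by an unstated survey under the 50% rule

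*Protocol article*

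**What the plan says.** All references are to the protocol article.

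- **Secondary outcomes** defines the Flanker measures: "The response time and correct rate for 50 tasks, including congruent and incongruent tasks, will be measured". Correct rate is therefore one of two measured quantities.
- **Analysis of secondary outcomes** applies the primary model to the continuous secondary outcomes, including "each element of the Flanker test, side-to-side movement, and each SDQ score for mental health". The same section then states the main exclusion: "participants who fail to reach a correct rate of 50% will be excluded on the assumption that they do not understand the test". No survey is named.
- **Subgroup analysis** adds a fifth analysis, made after "excluding participants whose correct rate on the Flanker test is below 80% at either the baseline or endline surveys". It does not say which outcomes this analysis covers.
- **Analysis of the primary outcome** says that "an intention-to-treat approach will be adopted to evaluate the impact on the primary and secondary outcomes".
- On timing, **Secondary outcomes** says "Randomized allocation is done in February 2018 and baseline data collection will be done from February to April 2018", with the intervention starting in April 2018, and "Post-intervention data will be collected between November and December 2018". Endline is thus after the intervention.

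No Flanker analysis that keeps every tested child is named.

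**The concern.** A rule that drops children because of a value measured after the intervention lets the intervention influence who is analysed. If the program raises accuracy, fewer intervention children than control children fall below the cut. Both arms lose low scorers, but not the same ones. The children left in the intervention arm then include some who would have been dropped had they been controls.

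This has two consequences. The accuracy contrast is expected to shrink, because the cut removes the part of the distribution where the arms differ in membership. Response time can show a difference without any true effect, because the retained children differ in ability between arms.

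The **Background** section gives executive function as the target cognitive function because it is held to predict academic achievement best. A diluted accuracy estimate could suggest that this pathway is inactive when it is not.

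**Working it through.** The article states no figure for the Flanker outcomes, so there is none to reproduce. It also gives no accuracy distribution, effect size or exclusion rate. Every size below rests on assumptions.

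**Step 1. What each rule permits.**

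| Rule | Survey that counts | Can an endline value exclude a child? |
|---|---|---|
| Below 50% (main Flanker analysis) | not stated | yes, unless baseline only is meant |
| Below 80% (fifth subgroup analysis) | baseline or endline | yes, explicitly |

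**Step 2. Single endline comparison.** Assume control accuracy is standard normal, intervention accuracy is shifted by d = 0.2 SD, and a common cut c removes a share q of controls, so c = Φ⁻¹(q).

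- Mean of retained controls: φ(c)/(1 − q)
- Share of the intervention arm removed: Φ(c − d)
- Mean of retained intervention children: d + φ(c − d)/(1 − Φ(c − d))

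For q = 5%: c = −1.645. The control mean is 0.1031/0.95 = 0.109. The intervention mean is 0.2 + 0.0728/(1 − 0.0325) = 0.275. The difference is 0.167.

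| Controls removed | Intervention removed | Control mean | Intervention mean | Effect left | Loss |
|---|---|---|---|---|---|
| 5% | 3.3% | 0.109 | 0.275 | 0.167 | 17% |
| 15% | 10.8% | 0.274 | 0.408 | 0.134 | 33% |
| 30% | 23.4% | 0.497 | 0.601 | 0.104 | 48% |

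**Step 3. A model closer to the plan.** This simulation used 1,000,000 children per arm. Each child has a normal latent ability at two surveys (correlation 0.5) and a binomial count out of 50 tasks. The treatment effect is 0.3 on the logit scale, at endline only. The estimate is the difference in change between arms. School clustering was left out because it does not drive this bias. The table assumes that all children benefit; the three values are for control mean accuracy of 0.88, 0.80 and 0.71.

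| Rule | Controls excluded | Intervention excluded | Share of true accuracy effect kept |
|---|---|---|---|
| 50%, baseline only | 2.0 / 8.3 / 17.5% | 2.0 / 8.3 / 17.5% | 98 / 96 / 94% |
| 50%, endline only | 2.0 / 8.3 / 17.6% | 1.1 / 5.4 / 12.3% | 87 / 76 / 69% |
| 50%, either survey | 3.6 / 14.3 / 28.1% | 2.8 / 12.0 / 24.5% | 85 / 71 / 60% |
| 80%, either survey | 27.9 / 52.3 / 70.9% | 24.2 / 47.8 / 66.8% | 43 / 29 / 23% |

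**Step 4. Response time.** It was simulated with no true effect and a correlation of −0.5 with ability. A spurious difference of about +0.01 to +0.04 SD appears under the 50% rule when endline counts, and of +0.035 to +0.052 SD under the 80% rule. Under the 50% rule on baseline only it is essentially zero.

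**Step 5. Other patterns of benefit, at mean accuracy 0.80.** If only weaker children benefit, 59% of the effect is kept (50% rule, either survey) and 15% (80% rule). If only stronger children benefit, 90% and 55% are kept. With no treatment effect, exclusions and means stay balanced under every rule.

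**The case against.** **The 50% rule may mean baseline only.** This stands. On that reading the arms lose equal shares and the comparison remains a randomised one. The estimate can still move, because the population is restricted: in the simulation it rose to 1.10 times the full effect when only stronger children benefited. A reader might infer that randomised comparability is broken in the main Flanker analysis, or that any accuracy effect must shrink. The text supports neither. For that analysis the defect is an unstated survey.

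**The largest losses belong to a supplementary analysis.** This also stands. The 80% rule sits among the subgroup analyses, and applying it to correct rate is an inference, since the article does not list the outcomes it covers.

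**The sizes are assumed.** They are. Accuracy on 50 tasks is a bounded count and need not be normal, and Step 2 compares endline only while the plan models change. Truncation also narrows the spread: divided by the retained controls' SD (0.900, 0.800, 0.702), the effects left are about 0.185, 0.167 and 0.148, which are losses of about 7%, 16% and 26%. The direction does not depend on this.

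**The exclusion is a validity screen, not a breach of intention-to-treat.** In part. The article explains its approach chiefly as keeping children in their allocated arm after a school move, and the 50% rule is justified by failure to understand the test. But a low endline score can also reflect poor inhibitory control, which is what the test measures. The tension with a strict reading of intention-to-treat remains.

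**Guessing.** A reader might infer that 50% is chance level and so fails to screen out guessers. That needs a task with two response options, which the article does not state, so the point is not made here.

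**Conclusion.** The concern holds in a limited form. The 80% analysis selects children on a post-intervention value of an analysed outcome. The 50% rule leaves open whether it does the same. No analysis of all tested children stands beside them.

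The harm requires two conditions: an endline value can exclude a child, and the program changes accuracy. The accuracy effect is then expected to shrink, and response time may carry a small bias (up to about 0.05 SD in the simulation). When either condition fails, the arms stay comparable. In particular, the rules create no false accuracy effect where there is none.

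The size is illustrative. It is modest for the 50% rule if few children score that low, and larger for the 80% rule if many fall below it. A reader might infer that the trial's main conclusion is at risk. It is not: the Flanker measures are secondary outcomes, which the article treats as exploratory, and the primary academic outcome does not use these exclusions. The change is worth making because it removes an avoidable bias at almost no cost.

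**What to change.** 1. Make the analysis of correct rate in all tested children, with no accuracy exclusion, the main Flanker accuracy analysis.
2. For response time, base any comprehension exclusion on the baseline test only, and say so in the rule. Allocation precedes baseline collection and the intervention starts in April, so confirm that each child's baseline test was taken before the first session.
3. Report the number excluded under each rule by arm.
4. Keep any endline-based 50% or 80% exclusion only as a labelled sensitivity analysis. State which outcomes the 80% analysis covers, and list it as an exclusion analysis rather than a subgroup.

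The change is to wording and needs no further measurement. The cost is slightly more noise from children who did not understand the endline test. The practice described as "Before the actual test, every student will do a practice test consisting of ten tasks once or twice" may limit this, although no pass mark is stated for it.

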#### Subgroup analysis

The effect of the intervention will be further analyzed using four subgroup analyses. The first subgroup analysis will focus on the location of the schools (urban and non-urban areas), the second on gender, and the third on baseline physical fitness performance using the median score on a 20m shuttle run. The fourth subgroup analysis will focus on baseline academic achievement using the total score on the national year-end examination in May 2017 and the median score. The fifth subgroup analysis will be done after excluding participants whose correct rate on the Flanker test is below 80% at either the baseline or endline surveys.

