### Sample size

Some 2445 children are enrolled in fourth grade at public elementary schools in the Sukhbaatar district of Ulaanbaatar, Mongolia. 2337 children are enrolled in the ten schools that participate in this study. All the eligible children will be recruited.

This study is a longitudinal cluster randomized trial which has three-level cluster units: the school, individual, and measurement time point. Additionally, the number of students at each school differs. To calculate the statistical power, we implemented a simulation study extending the method of a previous study to adjust for unbalanced data. [40] We assumed the standardized difference of the primary outcome to be equal to 0.2, and the dropout rate to be equal to 5%. Since the statistical power of the longitudinal cluster randomized trial depends on the correlation between measurement time points for the same individual, we assumed values of 0.4, 0.5 or 0.6. Bonferroni correction was used to adjust for the multiplicity of statistical testing calculated for each site (Urban/*ger*/mixed residential). Table 1 shows the statistical power and alpha error for each site. We also simulated the disjunctive alpha error and power. In all assumption settings, the disjunctive alpha error is kept nearly equal to 0.05, and the statistical power of the urban site exceeds 0.8. Additionally, under conditions in which the correlation equals 0.6, the statistical power exceeds 0.8 for both sites. The simulation was done 5000 times using the mixed procedure with SAS Software 9.4 (SAS Inc., Cary, NC, USA).

**Table 1 Tab1:** Simulation results of statistical power

Correlation	Disjunctive: 5000 simulations Standardized difference = 0.2					
	Alpha error			Power		
	Total	Urban	*Ger* or mixed residential	Total	Urban	*Ger* or mixed residential
0.4	0.050	0.027	0.024	0.957	0.871	0.642
0.5	0.047	0.023	0.024	0.977	0.920	0.719
0.6	0.047	0.023	0.024	0.992	0.967	0.814

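### Cutting baseline fitness and baseline achievement at the sample median discards information on whether the effect depends on baseline level; a continuous interaction would keep it at almost no cost

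*Protocol article*

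**What the plan says.** The Subgroup analysis section of the protocol article sets "the third on baseline physical fitness performance using the median score on a 20m shuttle run", and the fourth analysis on "baseline academic achievement using the total score on the national year-end examination in May 2017 and the median score". The natural reading is that each score is split into a lower and an upper half at the sample median. No reason is given for the cut, and no test, significance level or power is stated for these analyses.

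The same measures stay continuous elsewhere. The section on secondary outcomes lists "the continuous outcomes of BMI, sleeping hours, 20m shuttle run" among the variables for the linear mixed model, and it analyses the mathematics and language scores by the same method. Under Primary outcome, the May 2017 score is also the baseline value of the primary outcome.

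**The concern.** The two analyses ask whether less fit or lower-achieving children gain more, or less, from the programme. A median split treats a child just above the median like the fittest child and unlike the child just below. The cut-point is set by who happens to enrol, so it carries no fixed fitness or educational meaning.

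These are the only planned analyses by baseline fitness or achievement. The fitness question also follows from the trial's own rationale: the Intervention section says the music and spoken instructions are meant especially for children who are poor at physical activities. If the benefit does change gradually with baseline level, the split makes it more likely that the gradient is missed.

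**Working it through.** **Inputs from the article.** The Sample size section states that "2337 children are enrolled in the ten schools that participate in this study" and assumes 5% dropout, so N = 2337 × 0.95 = 2220. For the correlation ρ between time points, "we assumed values of 0.4, 0.5 or 0.6". The assumed effect is 0.2 SD. For the primary analysis, "A significance level of 0.025 will be set for a two-sided test".

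**Assumptions added here.** Two-sided 0.05 for the subgroup tests; equal arms; academic score as the outcome; a normal baseline score; no school-level variance in change; and an effect that changes by b = 0.05, 0.10 or 0.15 SD per SD of baseline. The article gives no gradient.

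**Step 1: reproduce Table 1.** Take the before/after change with variance 2(1−ρ), so SE = 2√(2(1−ρ)/n) and power = Φ(0.2/SE − 2.241). Children per stratum are not given. An urban share of 63.5% (1410 urban, 810 other) was fitted.

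| ρ | Urban: computed (stated) | *Ger* or mixed: computed (stated) |
|---|---|---|
| 0.4 | 0.882 (0.871) | 0.640 (0.642) |
| 0.5 | 0.935 (0.920) | 0.728 (0.719) |
| 0.6 | 0.975 (0.967) | 0.827 (0.814) |

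All six agree within 1.5 points with one fitted input. The variance model, including no school-level variance in change, is therefore consistent with the article's own simulation.

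**Step 2: information kept by a median split.** For a normal score and a linear gradient, relative efficiency is the squared correlation between the score and its split: 2/π = 0.637. About 36% is lost, which is like needing 1/0.637 = 1.57 times the sample.

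**Step 3: baseline shuttle run.**
- Continuous: estimate b, SE = 2√(2(1−ρ)/N).
- Split: difference between halves 2b√(2/π), SE = 4√(2(1−ρ)/N).

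At ρ = 0.5 and b = 0.10:
- Continuous: 0.10/0.0424 = 2.356, and Φ(2.356 − 1.960) = 65.4%.
- Split: 0.1596/0.0849 = 1.880, and Φ(1.880 − 1.960) = 46.8%.

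Power of the interaction test, continuous v split (%):

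| b | ρ = 0.4 | ρ = 0.5 | ρ = 0.6 | Points lost |
|---|---|---|---|---|
| 0.05 | 18.8 v 13.5 | 21.7 v 15.4 | 26.0 v 18.2 | 5 to 8 |
| 0.10 | 57.6 v 40.4 | 65.4 v 46.8 | 75.0 v 55.6 | 17 to 19 |
| 0.15 | 89.7 v 73.0 | 94.2 v 80.5 | 97.7 v 88.3 | 9 to 17 |

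Simulation at b = 0.10 (1500 runs per setting) gave 56.3 v 39.7, 65.6 v 46.7 and 74.9 v 55.3.

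**Step 4: baseline achievement.** Step 3 does not carry over, because the modifier is the baseline of the outcome and is correlated with the change by construction (slope ρ−1).
- 2018 score modelled on the continuous 2017 score: residual variance 1−ρ².
- Before/after change by median half: residual variance (1−ρ)²(1−2/π) + 1−ρ².

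At ρ = 0.5 these are 0.75 and 0.25 × 0.363 + 0.75 = 0.841. With b = 0.10:
- Continuous: 0.10/0.0368 = 2.720, power 77.6%.
- Split: 0.1596/0.0778 = 2.050, power 53.6%.

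For ρ = 0.4, 0.5 and 0.6 the results are 72.9 v 47.9, 77.6 v 53.6 and 83.8 v 61.4, a gap of 22 to 25 points (simulation, 2000 runs: 71.5 v 46.8, 76.6 v 54.3, 83.4 v 61.6).

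Part of this gap comes from adjusting for the 2017 score, not from removing the cut. If the halves were compared in the same adjusted model, the split SE at ρ = 0.5 would be 4√(0.75/2220) = 0.0735. That gives 0.1596/0.0735 = 2.171, power 58.3% and a loss of about 19 points.

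**Step 5: sensitivity.** Where the continuous test has 80% or 90% power at 0.05, the split loses:
- normal baseline: 19.2 or 16.6 points;
- uniform: 12.0 or 9.8;
- moderately skewed gamma: 22.2 or 19.6;
- exponential: 30.7 or 28.7.

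At two-sided 0.025 the normal-baseline losses are 21.4 and 18.5 points. If the effect instead stepped at the median by 0.2 SD (ρ = 0.5), the split would win: 65% v 46% by simulation.

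**The case against.** A median cut named in advance gives two equal groups, rules out an outcome-driven cut-point and is easy to explain to schools. It introduces no bias into the primary analysis and contradicts nothing in the article. All of that stands, and it keeps the point minor. It does not justify the cut as the test of effect modification, because the halves can still be shown beside a continuous analysis.

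The Subgroup analysis section also names no interaction test; an unseen analysis plan may add one. So no planned test with a stated power has been shown to fall short. The figures compare two ways of testing the same question. The choice to cut at the median is nevertheless written in the article and is not a detail left open.

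Three stronger readings are tempting and are not supported:
- A reader might infer a flat cost of 17 to 20 points. For the shuttle run, 17 to 19 holds at an assumed gradient of 0.10 SD per SD with a normal baseline. At 0.05 both analyses are weak and the loss is 5 to 8 points.
- A reader might take these to be the trial's only analyses of which children benefit. School location and gender are also planned subgroups, and location is in the primary model.
- A reader might suppose that the continuous analysis always wins. The ranking reverses if the effect truly steps at the median, though the article gives no reason to expect that.

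**Conclusion.** The concern holds as a cheap improvement to two supplementary analyses. With a roughly normal baseline and an approximately linear gradient, the median split gives up about 36% of the information on effect modification. Under the assumptions listed, the power lost on the shuttle run ranges from about 5 to 19 points across gradients of 0.05 to 0.15. For achievement at 0.10 the difference from the adjusted continuous model is about 22 to 25 points.

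These sizes rest on gradients, a baseline distribution and a significance level that the article does not state. School-level variation in how the effect depends on baseline would lower power for both analyses. The primary estimate, its significance level and the sample size are not touched.

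**What to change.** For the third and fourth subgroup analyses, test effect modification with the baseline score as a standardised continuous variable, and report the change in effect per SD with a confidence interval.

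- **Shuttle run:** add the baseline score to the mixed model with its interactions with time and with group × time, plus the lower-order terms these need.
- **Achievement:** model the 2018 score on group, the continuous 2017 score and their interaction, with the school random effect. The 2017 score is then not both a response and a modifier, as it would be in the two-time-point model.

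Check linearity with a quadratic or spline term, and keep the median halves for display only.

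The cost is a few sentences of analysis wording, with no new data. The drawbacks are an assumed linear gradient, which can be checked, and a result slightly less simple to present than two halves.

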### Primary outcome

The primary outcome of academic achievement will be assessed by the participants’ performance on the examination in 2018, which consists of a mathematics and Mongolian language portion. The participants’ score on the test for May 2017 at the end of third grade will be used as the baseline data.

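### Within the achievement halves, standard errors are too small: the May 2017 exam is both the cut and the starting score, in a model with no school-level variance in change

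*Protocol article*

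**What the plan says.** Under Primary outcome, the protocol article makes the May 2017 exam the starting value: the "score on the test for May 2017 at the end of third grade will be used as the baseline data". Under Analysis of the primary outcome, it compares "performance on the national year-end examination before and after the intervention using least squares means estimated by the interaction term" of group, time point and site. The starting score is therefore a row of the outcome, not a covariate. The variance structure is brief: "The random effects are school and individual". There is no school-by-time term. Analysis of secondary outcomes carries the same method to other continuous outcomes, including the shuttle run.

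Subgroup analysis then defines one split by "baseline academic achievement using the total score on the national year-end examination in May 2017 and the median score" and another by "baseline physical fitness performance using the median score on a 20m shuttle run". It names no different model. It does not say whether the median is taken over all children or within each school. Under Allocation, ten schools are balanced on residential area and size, not on achievement.

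**The concern.** A child selected for a low May 2017 score tends to drift back towards the mean of their own school. A low scorer from a strong school rebounds further than a low scorer from a weak school, and a high scorer from a strong school falls back less. If the schools in one arm happen to be stronger, that arm shows a better change in both halves even when the programme does nothing. In the full sample the stable school differences cancel from the change; after selection on the starting score they do not.

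With ten schools and no balancing on achievement, some imbalance is expected. The trial could report that the programme helps, or harms, low achievers or both halves when only school intake differs, with an interval too narrow to warn the reader.

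**Working it through.** **Inputs from the protocol article.** Sample size: 2337 children in ten schools, effect 0.2 SD, 5% dropout, within-child correlation 0.4, 0.5 or 0.6. Allocation: six urban and four *ger* or mixed schools. Primary analysis: "A significance level of 0.025 will be set for a two-sided test"; no level is stated for subgroups.

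**Assumed.** School ICC 0 to 0.20 (not stated); individual school sizes (only a range is given); an overall median; the primary model applied within each half; no intervention effect and no true school-by-time variation.

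**1. The plan's own figure.** Take the SD of change as √(2(1−ρ)), 0.95N/2 children per arm, two-sided alpha 0.025, and an urban/other split of 1488/849. The split is not stated and was fitted. At ρ = 0.5 the SD of change is 1.
- Urban: n = 706.8 per arm; 0.2/√(2/706.8) = 3.76; power = Φ(3.76 − 2.24) = 0.936 (Table 1: 0.920).
- Other: n = 403.3 per arm; 0.2/√(2/403.3) = 2.84; power = Φ(2.84 − 2.24) = 0.725 (Table 1: 0.719).
- Either site: 1 − (1 − 0.936)(1 − 0.725) = 0.982 (Table 1: 0.977).

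All nine power cells come within two percentage points. Table 1 is therefore consistent with a change contrast that carries child-level error only.

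**2. False effect for a given imbalance.** Let D be the arm difference in stable mean score, in within-school SDs, and r the within-school correlation. For normal scores cut at the overall median, the expected false effect, with the same sign in both halves, is

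(1 − r) × [φ(D/2)/Φ(−D/2) − φ(D/2)/Φ(D/2)].

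- D = 0.2: the bracket is 0.397/0.460 − 0.397/0.540 = 0.127, giving 0.076, 0.064 and 0.051 SD at r = 0.4, 0.5 and 0.6.
- D = 0.3: the bracket is 0.3945/0.4404 − 0.3945/0.5596 = 0.191, giving 0.114, 0.095 and 0.076 SD.
- Full-sample change: 0.

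With five schools per arm, the chance SD of D is √(2 × ICC/5), which is 0.20 at ICC 0.10. A difference of 0.2 SD is then one standard deviation of ordinary imbalance.

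**3. Effect on the test.** In null simulations at ρ = 0.5 and ICC 0.10, the estimate in the low half varied with SD 0.089 while the model's standard error was 0.055. The implied rejection rate at nominal 5% is 2 × [1 − Φ(1.96 × 0.055/0.089)] = 2 × [1 − Φ(1.21)] = 0.226, as simulated. At ICC 0.20 the SD is 0.119, implying 2 × [1 − Φ(0.906)] = 0.365 (simulated 0.359). In the full sample at ICC 0.10 both quantities were 0.043. On a simulated data set, a mixed-model fit with child random intercepts and school terms gave the same result as the change analysis (low half 0.0512, standard error 0.0568), so school intercepts do not absorb this variation.

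Rejection with no true effect, nominal 5%, ρ = 0.5:

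| School ICC (assumed) | 0.02 | 0.05 | 0.10 | 0.20 |
|---|---|---|---|---|
| Either half, planned model | about 0.08 | about 0.14 | about 0.22 | about 0.35 |

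- Full sample, planned model: 0.04 to 0.06 throughout.
- At ICC 0 the halves reject at 0.05.
- At ICC 0.10 the rate in a half is about 0.25 at ρ = 0.4 and 0.17 to 0.18 at ρ = 0.6.
- At nominal 0.025, ρ = 0.5 and ICC 0.10, it is about 0.16.
- Halves within a single site behave similarly (0.20 to 0.23 at ICC 0.10, nominal 5%).

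**4. What changes the result (ρ = 0.5).**
- Same change score, tested on school means with 8 degrees of freedom: 0.04 to 0.06 at ICC 0.02 to 0.20.
- Follow-up score adjusted for the starting score, child-level error: 0.14 to 0.56 over the same ICCs.
- Low-versus-high interaction, planned model: about 0.05 to 0.08 up to ICC 0.10, about 0.14 at ICC 0.20.
- Halves cut at each school's own median, ICC 0.10: about 0.07.

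**5. Why baseline adjustment does not remove the artefact.** Given the starting score, the expected follow-up still contains (1 − r) times the school mean, so an imbalance D leaves (1 − r) × D. For D = 0.3 this is 0.18, 0.15 and 0.12 SD at r = 0.4, 0.5 and 0.6, larger than the 0.114, 0.095 and 0.076 in step 2.

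**The case against.** **The text does not fix the analysis.** The article does not say that the primary model is refitted within halves, or which median is used, and a full analysis plan may settle both. This stands as a condition on the finding. But the article describes only one model for continuous outcomes and introduces the subgroups as a further analysis of the effect, so the reading is the natural one.

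**Using one score as both cut and starting value is not in itself the fault.** This stands. The identical change score, tested with school-level error, holds its level. What fails is the error term: selection creates school-level variation in change, and the model has nowhere to put it.

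**The subgroup question is whether the halves differ, and that contrast is largely sound.** This stands up to an ICC of about 0.10. The article does not state that the claim will rest on the interaction, so effects within halves remain open to being read on their own.

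**Stakes are limited.** This is one supplementary analysis. At ICC 0.02 the inflation is modest, and at zero there is none. The shuttle-run version follows from the same reasoning but was not simulated.

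**Conclusion.** The point holds in this form: if the described model is applied within halves cut at an overall median, its standard errors there are too small. Nominal 5% tests reject in about 8% to 35% of null trials for ICCs of 0.02 to 0.20 at correlation 0.5. The size depends on an ICC that the protocol does not give, and on the two readings named above.

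Three stronger conclusions are tempting but not supported.
- A reader might infer that the median split biases the subgroup effects. Schools are allocated at random, so the artefact averages to zero over randomisations. It can mislead in either direction in the one trial that is run, because its uncertainty is not counted.
- A reader might infer that taking the May 2017 score out of the outcome and adjusting for it cures the problem. Steps 4 and 5 show that it leaves a larger false effect for the same imbalance, and rejects more often unless school-level error is added.
- A reader might carry the fault over to the primary analysis. This mechanism leaves the full-sample change contrast at its nominal level.

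**What to change.** In Subgroup analysis, state the following for the achievement split, and for the shuttle-run split when the shuttle run is the outcome.

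1. The subgroup claim rests on the group-by-time-by-subgroup interaction, with its confidence interval, from one model fitted to all children.
2. Effects within each half are reported only with school-level error. Either give that model random terms for school-by-time and school-by-subgroup-by-time, or analyse school-mean changes in each half with school-level degrees of freedom. The second option is simpler with ten schools, and it is the one shown above to reject at 0.04 to 0.06.
3. State whether the median is overall or within school. A split at each school's own median can be added as a sensitivity analysis, since it removes most of the artefact.
4. Do not offer baseline adjustment as a substitute for school-level error.

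This needs a few lines of wording and no new data. The price is wider subgroup intervals, because they will carry the between-school variation that the present model leaves out.
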